## Interventions

### Explanation for the choice of comparators {6b}

As inpatient treatment may not be the best treatment option for all participating patients, the comparator is not the usual rehabilitation application. Treatment-as-usual was chosen as a comparator to enable a comparison with actual care. Patients in the control group will continue to receive usual care by their attending PCP. It will be possible for them to apply for rehabilitation treatments (MT/NMSM) using paper-based forms.

### Intervention description {11a}

Multidisciplinary care planning for patients allocated to the intervention group will follow a digital case management approach, which allows flexible and clinical-based decision-making. In this complex intervention [19], case conferences (CC) will be arranged on the digital communication platform Cankado [24]. Stakeholders from different disciplines and holding different roles will be involved in the CCs:PCPs will be experts for their patients, enter them on the digital communication platform and provide for the rehabilitation relevant medical information about them. They will make an initial proposal for a treatment (MT/NMSM) which will be discussed on the platform with the stakeholders. Once the discussion about appropriate treatments (MT/NMSM) reaches consensus, the attending PCP will propose and discuss the treatment option (MT/NMSM) with the patient.A case administrator, employed by the German pension insurance, will facilitate the communication between the stakeholders and support cooperation if necessary. If the patient agrees to the treatment proposal (MT/NMSM) from the CC, it will be the case administrator’s task to arrange the appropriate programme.A public health physician, also employed by the German pension insurance and experienced in rehabilitation care planning, will also attend the CC and can recommend appropriate measures (MT, inpatient rehabilitation treatments, outpatient therapies) from pension insurance services.To offer a different and non-clinical perspective, an employee of the employment agency or jobcentre will also participate in the CC and can suggest appropriate NMSM and more work-related services from their portfolio, like vocational training, requalification or rehabilitation.If a specific need is identified by stakeholders in the CC, patients can receive support from a social worker in accessing treatments (MT/NMSM). The social worker is also employed by the German pension insurance and will not be involved in the CC itself.

The digital CC is designed to facilitate rehabilitation care planning for PCPs as well as patients and to improve the quality of care through different components:Efficient, multidisciplinary communication of stakeholders. Usage of the digital communication platform Cankado [24] will enable communication without the need for a meeting. A text box offers the option to respond to other stakeholders’ comments and suggestions, which ensures time flexibility and facilitates fast response processes.Tailoring and flexibilisation of treatments (MT/NMSM). Care planning for patients can contain regular or innovative treatments (MT/NMSM). Innovative treatments (MT/NMSM) can include services from the employment agencies or job centres that are usually not funded by the German pension insurance. It will be also possible for patients to receive treatments (MT/NMSM), for which they do not meet the requirements in routine care (e.g. insufficient insurance participation period). The multidisciplinary perspective and the possibility for individualisation enable tailored treatment (MT/NMSM) offers based on flexible clinical decisions.Possibility for additional support (e.g. assisting the patient in coordinating treatments, appointments or transport or planning absences from the family) through the involvement of a social worker.

An intervention description based on the TIDier checklist [25] is presented in Additional file 3. Also, a logic model was created in keeping with MRC guidance [26] and the W.K. Kellogg Foundation [27], providing a theoretical framework for the intervention (Fig. 1).

**Fig. 1 Fig1:**
[figure not shown]
Logic model

### Criteria for discontinuing or modifying allocated interventions {11b}

PCPs as well as patients will be able to withdrawal consent for study participation (e.g. in case of deterioration of health condition) at any time without giving reasons or experiencing any disadvantages. Modifying allocated interventions is not applicable as care planning is meant to be flexible.

### Strategies to improve adherence to interventions {11c}

The case manager will monitor adherence for PCPs in the CC. In the event of difficulties (e.g. delayed processing, missing information on the platform), the study team will be informed and contact the PCP to provide flexible support if required. The case manager also monitors the completeness of the additional questionnaires from patients in the intervention group (see SPIRIT item 18a) on the platform. The social worker can assist patients from the intervention group with all organisational issues regarding the intervention. As part of the monitoring and control process, meetings with the trial steering committee will be held every 14 days to discuss deviations and violations of the protocol and to assess the risk of such (composition of the trial steering committee is explained in SPIRIT item 5d). Adherence to resulting treatment decisions (MT/NMSM) will not be monitored, as the focus of the trial lies on the procedures of the CC. However, if needed, the social worker can be administered to support patients in taking up the offer.

### Relevant concomitant care permitted or prohibited during the trial {11d}

Patients with ongoing application procedures for rehabilitative services cannot participate in the study. Patients from the control group will be able to apply for rehabilitation treatments (MT/NMSM) in the regular way. Apart from this, the study protocol does not restrict access or referral to any usual care services.

### Provisions for post-trial care {30}

The aim of the intervention is to facilitate access to appropriate rehabilitative treatments (MT/NMSM) for patients at high risk of early retirement. After the trial, all participants will return to routine care. If there will be a continuing need for healthcare, this can be discussed with the attending PCP and appropriate steps taken. This will be independent of the intervention given. Post-trial care will not be provided as part of the study.

### Outcomes {12}

The primary outcome is the total numbers of days of sick leave between t1 and t2 (12-month period after the assumed completion of treatment (MT/NMSM)). The time points for assessments are presented in Table 1.

#### Primary outcome

Number of days of sick leave: postal enquiry health insurance (time periods inquired: 6 months before baseline till t0, t0 till t1, t1 till t2). Patients will receive a prepared form and a stamped envelope so that the request can be sent to their health insurance directly after signature. The aggregation method for both groups will be the mean number of sick days between t1 and t2 assessed at t2.

#### Secondary outcomes

Number of days of sick leave: self-report (time periods inquired: 6 months before baseline till t0, t0 till t1, t1 till t2). The aggregation method for both groups will be the mean number of sick days between t1 and t2 assessed at t2.Work ability: assessed using the German version of the WAI [20], which indicates the extent to which an employee is capable of performing his or her job under the individual conditions of their own health and the circumstances of the workplace. WAI scores are ranging from 7 to 49 and can be categorised into excellent (44-49), good (37-43), moderate (28-36) or poor (7-27) work ability. The aggregation method for both groups will be the mean WAI scores at t2.Health-related quality of life: measured with the German version of the SF-36 [21, 22], which assesses subjective health on eight dimensions that can be assigned to two sum scales, physical and mental health. SF-36 scores are ranging from 0 to 100, with higher scores indicating better subjective health. We will use the German norm sample from 1994 to determine the sum scales [22]. The aggregation method for both groups will be the mean SF-36 scores at t2.

#### Process evaluation

Withdrawal rates: withdrawals and reasons will be documented during the course of the studyTime between baseline and start of first treatment (MT/NMSM, in days): patient questionnaire about start and end dates of treatments (MT/NMSM; t1, t2)Treatment (MT/NMSM) recommended on the digital communication platform (only intervention group): recorded on digital communication platform (innovative treatment: yes/no; free text on the final decision)Treatments (MT/NMSM) used: patient questionnaire (free text and categorical classification of the treatment; t1, t2)Involvement of social worker and reasons for involvement (only intervention group): recorded on digital communication platform (yes/no)Duration of CC (in days, only intervention group): data from digital communication platformQualitative Interview data on facilitating and hindering factors that influence the success of the intervention and help to identify adaptations that are necessary for successful implementation.

### Participant timeline {13}

Eligible PCPs will be asked to sign informed consent (Additional file 2) and then complete a short questionnaire containing demographic and practice characteristics. Afterwards, they will start screening for eligible patients. Data will be collected at three time points: baseline (t0), 6 months (t1) and 18 months (t2) during personal or telephone appointments with a research assistant. We expect CCs or other application procedures, waiting times and possible treatments (MT/NMSM) to be completed 6 months after baseline (t1). The time schedule of patients' enrolment, interventions, and assessments is displayed in Table 1.

**Table 1 Tab1:**
[figure not shown]
Time schedule of patients’ enrolment, interventions and assessments

*HADS* Hospital anxiety and depression scale, *WAI* Work ability index, *SF-36* Short Form 36 Health Survey, *MT* Medical treatment, *NMSM* Non-medical support measures

Interviews with PCPs will start earliest after closure of the CC of their first patient allocated to the intervention group and are planned to be conducted at various time points in order to provide a broad picture. Interviews with patients will also take place at different time points, but no earlier than after the offer of treatment (MT/NMSM). Other persons involved in the CC (public health physician, case administrator and social worker) will be asked for an interview at the end of the RCT.

### Sample size {14}

Based on a systematic review of workplace interventions to prevent work incapacity [27], a difference of 34 days of incapacity to work (12-month period between t1 (assumed end of treatments) and t2) between the intervention and control group is assumed and applied for sample size calculation. A sample size of 149 patients in each group will have 90% power to detect a difference in means of 34 days of sick leave assuming that the common standard deviation is 90 days using a two-group *t*-test with a 5% two-sided significance level. Assuming that about 15% will be lost to follow-up or withdraw from the study, 352 participants have to be included. If a PCP would recruit six participants, about 59 PCPs must participate in the study. Sample size calculation was performed using R: A Language and Environment for Statistical Computing [28] and the package pwr [29]. The number of patients to be recruited per practice (*n* = 6) is based on feasibility and experience regarding the reasonableness for participating practices.

Participating in the interview study, as a part of the process evaluation, will be optional. The sample size for interviews will depend on data saturation [30]. We plan on interviewing 12 to 25 PCPs and patients each. Persons involved in the CC (public health physician, case administrator, social worker) will also be invited for the interview.

### Recruitment {15}

PCPs will be recruited, using a research practice network, but additional practices will be contacted if needed. Practices will be approached by the study team by post, telephone, email or in person. In case of interest, study information can be sent and a personal information appointment will be arranged with a member of the study team. Prior to signing the consent form PCPs will have the opportunity to ask further questions. Consented PCPs will be asked to fill out the baseline assessment.

Potential patients will be identified by PCPs, via consultation or through the practice database, based on eligibility criteria. PCPs will be reminded to recruit eligible patients by members of the study team on a regular basis. Contact will be in person, by telephone or by mail. If recruitment numbers are low, PCPs will be asked about the difficulties and support that can be offered, e.g. in searching the practice database. PCPs will receive a compensation of 200 euros for study participation, and further 50 euros for each patient recruited. This allows for a maximum compensation of 500 euros. Contact with identified patients can be arranged flexibly by the PCPs and can be made in person by telephone or by post. PCPs will provide information about the study and check the eligibility criteria together with patients. Patients’ self-reports will be used for eligibility-checking. Eligible and interested patients can then contact the study team themselves or provide written consent for their PCP to pass on their contact details to the study team (Additional file 2). Eligibility criteria will be double-checked by the study team, by telephone or in person. Patients who are not eligible will not be able to participate in the study. As the identification and initial approach of potential patients takes place in the primary care practice, the exact number of patients screened will not be determined. For the CONSORT flow chart [23], the number of patients who will have given their written consent to be contacted by the study team will be used. The reasons for exclusion from the study programme, which will be determined by the study team during the double-check, are noted in a list. If interested and eligible, a personal appointment with a member of the study team will take place. The appointment is arranged according to the patient's needs and can be organised at the patient's home, the PCP`s practice or other suitable location. Patients will receive written study information and will have the possibility to ask questions. Once the patient signed informed consent (Additional file 2), the baseline assessment and randomisation will be completed. There will be no financial compensation for participating patients.

## Assignment of interventions: allocation

### Sequence generation {16a}

Eligible and consenting patients will be randomised after baseline assessment with a 1:1 allocation stratified by primary care practice and using permuted blocks of six (as this is the number of patients to be recruited in the practices).

Prior to the commencement of the trial, an algorithm was used to create random sequences and discarded if they were not balanced (1:1) or too trivial, to ensure concealment for as long as possible (till the randomisation of the last patient). One of the random sequences was then randomly assigned to each practice to be recruited. This procedure was carried out by an independent researcher who was not involved in the conduct of the study in any other way.

### Concealment mechanism {16b}

Randomisation will take place using the web-based application randomar [31], programmed by the independent researcher who also generated the randomisation sequence. The allocation of patients is conducted by computer-generated random sequence and is concealed from the study team, patients and attending PCPs until the time of randomisation, at least for the first five patients. For the recruitment of the last patient in a practice, however, the allocation can no longer be concealed. The allocation will be recorded in a database and can no longer be changed. The web-based application will be only accessible by trained members of the study team and protected by a password.

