A limitation is the randomisation technique stratified by primary care practice and using permuted blocks of six (as this is the number of patients to be recruited in the practices). By this design, allocation concealment will not be given for the last (sixth) patient recruited in a practice. This increases the risk of selection bias [43]. Another limitation of the chosen randomisation method is that not all PCPs may be able to recruit six patients. In this case, the equal distribution of patients to both groups would no longer be given. It can also be argued that spill-over effects may occur, as the focus of participating PCPs may have a greater emphasis on the rehabilitation care and intervention planning than without the study. This may also accelerate or initiate processes in the control group. Also, if the study finds differences between the groups, this would be even more indicative of an intervention effect. However, a spill-over effect could also hide the true effect (Type II error). In order to reduce spill-over effects, the use of cluster randomisation was also discussed. Ensuring the chronology of such randomisation (first recruitment, then randomisation) did not appear feasible in the context of the study (long recruitment periods lead to longer waiting times for patients). Without adherence to this chronology, there would be no allocation concealment at all and the risk of recruitment bias would be increased [44]. Therefore, we decided on the stratified randomisation. Also, an equal distribution of workload for PCPs is given.

Another limitation is, that there will be no control of whether the in the CC recommended treatments (MT/NMSM) are actually used. It should be noted that the intervention is particularly about the application and decision-making processes and the offer of treatments (MT/NMSM). Similarly, only these can be influenced within the framework of the study. However, when a person can actually participate in a rehabilitation or other intervention depends on a number of further factors, such as the availability of rehabilitation care slots.

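### Allocation is described as concealed for the first five patients in a practice, but with one 3:3 sequence of six the fifth is already certain in about 40% of the practices that reach a fifth patient

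*Protocol article*

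**What the plan says.** Under Sequence generation {16a}, randomisation is stratified by practice with "permuted blocks of six (as this is the number of patients to be recruited in the practices"). Candidate sequences were "discarded if they were not balanced (1:1) or too trivial, to ensure concealment for as long as possible (till the randomisation of the last patient"). The article does not define which sequences counted as trivial. It continues: "One of the random sequences was then randomly assigned to each practice to be recruited". A practice therefore works through a single fixed list with three patients per arm.

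Under Concealment mechanism {16b}, the allocation "is concealed from the study team, patients and attending PCPs until the time of randomisation, at least for the first five patients", followed by: "For the recruitment of the last patient in a practice, however, the allocation can no longer be concealed". The Discussion repeats this as a limitation: "allocation concealment will not be given for the last (sixth) patient recruited in a practice". It adds that this raises the risk of selection bias.

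Implementation {16c} has each result shown at once to the study team member and then reported to the attending physician. Who will be blinded {17a} says that patients and the study staff directly involved cannot be blinded.

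**The concern.** Conceding the sixth patient presupposes that someone knows the block length, the 3:3 split and the five earlier results. The same person can stop counting earlier: once three patients are in one arm, every remaining patient in that practice goes to the other. If this happens by the fourth patient, the fifth is known, and if by the third, the fourth is known too. The statement about the first five, and the limitation confined to the sixth, then understate the predictability.

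This matters because of how patients enter the trial. Under Recruitment {15}, physicians choose whom to approach, eligibility rests on patient self-report, and the unblinded study team does the second check. The number screened in the practices is not determined, so selective approach would not show in the CONSORT flow chart. A reader judging risk of bias would rely on the concealment statement as written.

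**Working it through.** **Inputs from the protocol article.** One sequence of six per practice, balanced 1:1 and so 3:3 ({16a}). Earlier results known to the study team and the physician ({16c}, {17a}). Planned total 352 with six per physician (Sample size {14}), so 352/6 = 58.7, or 59 practices.

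**Step 1: the admitted figure.** There are C(6,3) = 20 balanced sequences. Given 3:3 and five known results, the sixth is certain in 20/20 = 100%. This reproduces the plan's concession. The plan's implied figure for the fifth is 0%.

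**Step 2: the fifth patient.** The fifth is certain when the first four split 3:1:

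2 × C(3,3) × C(3,1) / C(6,4) = 6/15 = 40%.

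As a check by counting, this is the same as the last two allocations being identical, which holds for 2 × 4 = 8 of the 20 sequences. The implied 0% does not reproduce.

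**Step 3: the fourth patient.** The fourth is certain only if the first three are identical (AAABBB or BBBAAA): 2/20 = 10%.

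**Step 4: the undefined discard.** The table repeats the count under several readings of what was removed, for an observer who uses only the 3:3 balance and the earlier results. The excess is the expected number of certain allocations per full practice beyond the sixth. The last column multiplies it by 58.7 practices.

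| Sequences removed | Left | Fourth certain | Fifth certain | Excess per 6 | Of 352 |
|---|---|---|---|---|---|
| None | 20 | 2/20 = 10% | 8/20 = 40% | 0.50 | 29 |
| AAABBB, BBBAAA | 18 | 0% | 6/18 = 33.3% | 0.33 | 20 |
| Those and the two alternating | 16 | 0% | 6/16 = 37.5% | 0.375 | 22 |
| The two alternating only | 18 | 2/18 = 11.1% | 8/18 = 44.4% | 0.56 | 33 |
| Any run of three | 14 | 0% | 4/14 = 28.6% | 0.29 | 17 |
| Any ending in an identical pair | 12 | 0% | 0% | 0 | 0 |

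Without any discard, the excess of 0.5 of 6 is 8.3% of allocations.

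**Step 5: an observer who knows the discard rule.** Discarding then adds information. With AAABBB and BBBAAA removed, two identical allocations at the start fix the third patient, which happens in 33.3% of practices. Under the last row of the table, the first four always split 2:2. The fourth is then known in every practice and the third in one third, so 0.33 + 1 + 1 = 2.33 of 6 allocations are certain, counting the sixth.

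**The case against.** The strongest defence is the purpose given for the discard, which was to keep concealment until the last patient. If it removed every sequence ending in an identical pair, the fifth would never be certain from balance alone, and {16b} would hold for anyone unaware of the rule. No text says that physicians were told it, and an independent researcher made the sequences. This reading cannot be excluded, and it is why the share must be given as a range. But it needs an unstated filter that drops 8 of the 20 sequences, which is no longer an ordinary permuted block of six, and it moves the predictability to the fourth patient for anyone who knew the rule.

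Other mitigating points stand. The article discloses the weakness in kind and explains why cluster randomisation was rejected. Randomisation follows consent and baseline assessment, and a logged result cannot be changed. Patients may contact the study team themselves, so the physician does not fully control the order of entry. The primary model adjusts for sex, age, baseline sick leave and baseline WAI, which would absorb part of any selection on those measured factors.

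A reader might infer more than the documents support:

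- **A quarter of allocations known.** Under an unrestricted block 1.5 of 6 are certain, or 88 of 352. But 1 of those 1.5 is the sixth patient, already disclosed, and the count needs every practice to recruit six. The Discussion expects that some will not, and Trial status reports early termination for low recruitment.
- **A bias of several days.** An assumed difference of 20 to 40 days among determined patients, times 25%, gives 5 to 10 days. For the undisclosed part alone (0.5/6) it gives 1.7 to 3.3 days. The 20 to 40 days has no source in the documents, and the sum assumes selection of every determined patient.
- **Selection overlooked in the Discussion.** The remark there that a group difference would be all the more indicative of an effect concerns spill-over to controls. The selection risk is named separately.
- **No analysis planned.** Such an analysis could sit in the statistical analysis plan, which is not shown.

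**Conclusion.** The concealment statement in {16b} and the sixth-patient-only limitation in the Discussion are wrong for any ordinary permuted block of six. Among practices reaching a fifth patient, the fifth allocation is certain in 40% under an unrestricted block and in about 29% to 44% under common readings of the discard. The fourth is certain in about 10% at most.

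The excess over what is disclosed is about 0.5 of 6 allocations per full practice under an unrestricted block (29 of 352), with 17 to 33 across those readings. Real recruitment makes it smaller, because certainty arises only at the late positions that under-recruiting practices often do not reach.

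This rests on the block length, the 3:3 balance and the earlier results being known, which the plan already grants for the sixth patient. It shows an opportunity for selection, not that selection took place. The size of any bias cannot be derived from the documents. The sample size is unaffected.

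**What to change.** Correct {16b} and the Discussion to say that the sixth, often the fifth and occasionally the fourth allocation in a practice can be predicted. State which sequences the discard of trivial ones removed, so that the exact share can be computed.

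Before database lock, pre-specify a sensitivity analysis of the primary outcome with the same model, excluding patients whose arm was fully determined by earlier allocations in their practice. Add a comparison of baseline characteristics by arm for determined and undetermined patients. {16b} and {16c} say that each allocation is logged; the order of entry within practice is assumed to be recoverable from that log. The indicator can be derived after lock, so the statistician stays blinded while the analysis is being specified. The documents do not say whether lock has taken place. If it has, the analysis should be labelled post hoc.

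The cost is a text correction, a little extra analysis work and lower precision in that one analysis. At full recruitment under an unrestricted block it would drop 1.5 of 6 patients, widening the confidence interval by a factor of about 1/√0.75 = 1.15. The loss is smaller where practices stopped short of six.
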